**Conclusions:**

If the intervention proves successful, it may serve as an important tool for improving academics’ well-being, working life skills, and engagement by understanding how this intervention can help academic staff members with different initial burnout levels. In addition, it can help to understand and solve individual challenges related to well-being in the academic workplace.

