### Aims and Objectives

There is a need to enhance academics’ well-being, yet effective, research-based, and feasible tools are limited. Accordingly, this study pursues 4 goals. First, we aim to develop an online ACT-based intervention for academic staff that integrates working-life skills, specifically time management and reflective skills, and is feasible to complete within demanding work environments. Second, we aim to evaluate the intervention quantitatively by identifying latent burnout profiles among university staff and examining whether changes in burnout, psychological flexibility, perceived stress, overall well-being, and procrastination differ across profiles and participation formats. Third, we aim to examine participant engagement and retention by investigating whether dropout differs across latent burnout profiles and according to participation formats (individual vs group-based). Fourth, we aim to explore participants’ lived experiences of the intervention qualitatively, with a particular focus on psychological flexibility processes and on which of these processes’ participants perceive as most meaningful for their well-being and functioning at work.

Our research questions (RQs) are as follows:

RQ 1. What latent burnout profiles can be identified among staff at the University of Helsinki, and to what extent do the effects of the online ACT-based intervention differ between them?RQ 2. How do observed pre-post changes in burnout, psychological flexibility, perceived stress, and overall well-being vary across burnout profiles and participation formats?RQ 3. How do latent burnout profiles differ in training dropout rates, and does participation in group-based versus self-guided online ACT-based training relate to dropout?RQ 4. How do participants describe their experiences of psychological flexibility processes following participation in a digital ACT-based intervention, and which of these processes do they perceive as most meaningful in supporting their well-being and functioning in their work?

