## Methods

### Study Design

#### Mixed Methods Design

We will conduct a single-arm, nonrandomized, and mixed methods study with baseline, post-intervention, and 6-month follow-up assessments. Our study methodology description is based on the GRAMMS (Good Reporting of a Mixed Methods Study) reporting guidelines [38] and checklist (Checklist 1). A mixed methods approach is chosen, as the study aims to evaluate changes in participants’ well-being and related outcomes at the group level and to understand how participants experienced the intervention and its psychological flexibility processes at the individual level. An explanatory sequential design will be used, with priority given to the quantitative strand. Quantitative data will address latent burnout profiles (RQ 1), changes in outcomes, and dropout (RQs 2 and 3), whereas qualitative data will be used to explain, contextualize, and deepen these findings by examining participants’ final reflections, goal statements, and interview accounts (RQ 4). Although some qualitative material is generated during the course, qualitative interviews will be conducted after the main quantitative data collection phase.

Integration will occur at the interpretation stage once all data have been collected. Integration will be conducted by the researchers, involving the comparison and combination of quantitative findings (RQs 1‐3, changes in outcomes, burnout profiles, and dropout) with qualitative data (RQ 4, participant reflections and interviews). Through this, we will explore how quantitative patterns are potentially explained and contextualized by participants’ individual experiences, as well as identify possible convergence, complementarity, or divergence between the 2 data strands.

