### Analyses

#### Statistical Analyses

For RQ 2, the effects of the course are analyzed with repeated-measures ANOVA and hierarchical modeling to see the changes at the group level. In addition, for RQ 1, the participants will be clustered based on their initial burnout risk score to compare the effects of the course in different risk groups using latent profile analysis and repeated-measures ANOVA. For RQ 3, attrition analyses are conducted using chi-square tests of independence and odds ratios to examine whether dropout rates differ across latent burnout profiles and between group-based and self-guided participation formats.

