### Strengths and Limitations

This study’s key strength lies in its versatile mixed methods approach. First, by using latent profile analysis to profile participants’ baseline burnout scores (RQ 1), we explore burnout as a complex and heterogeneous construct and move beyond aggregated group-level averages to a more person-oriented perspective, which has gained more popularity in the last decades [52]. We aim to additionally explore participants’ self-reported changes during the course quantitatively (RQ 2) but also deepen and contextualize these findings with qualitative insights (RQ 4). This integration allows us to identify not only whether change occurs but also to explore how and why participants perceive change happens or does not happen, and whether qualitative experiences converge with or diverge from quantitative trends. Thus, the study may provide a more nuanced understanding of what participants experience during the course and which aspects may be most useful for them. Finally, we also aim to examine whether burnout profiles and the format of participation may influence engagement in the course (RQ 3), which may provide practical information regarding how and to whom the course may be most beneficial.

Furthermore, the study design also benefits from its flexibility, as well as its ease of execution and implementation in university work environments. As the study takes place in an online environment with no facilitation, a flexible schedule, and is continuously open, the study does not require excessive resources and is relatively easy to carry out. Additionally, the flexible design may mitigate some of the burden on participants, as they are able to complete the course at their own pace, thus also following ethical research principles.

However, the study design also possesses limitations. The flexible schedule design also indicates that a control group cannot be used, and thus we are not able to randomize participants, which precludes, for instance, a randomized controlled trial. A nonrandomized design may also introduce selection bias, which may limit the generalizability of the results. Therefore, the conclusions regarding the effectiveness of the course are limited.

A potential limitation of the mixed methods design is that qualitative data are collected from a subsample, which may not fully represent the broader quantitative sample, potentially limiting the integration of the findings and the generalizability of the results.

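### Burnout profiles are formed on the T1 score and then compared on burnout change without a control group, so regression to the mean can pass for a differing course effect

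*Protocol article*

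**What the plan says.** RQ 1 first asks which burnout profiles exist and then "to what extent do the effects of the online ACT-based intervention differ between them". The Statistical Analyses section answers this as follows: "the participants will be clustered based on their initial burnout risk score to compare the effects of the course in different risk groups". The tools it names are a latent profile analysis to form the groups and an ANOVA for repeated measures to compare them. The second aim includes burnout among the outcomes, "examining whether changes in burnout, psychological flexibility, perceived stress, overall well-being, and procrastination differ across profiles and participation formats". RQ 2 is worded more carefully: "How do observed pre-post changes in burnout, psychological flexibility, perceived stress, and overall well-being vary across burnout profiles and participation formats".

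The design is stated under Mixed Methods Design: "We will conduct a single-arm, nonrandomized, and mixed methods study with baseline, post-intervention, and 6-month follow-up assessments". Strengths and Limitations concedes that "a control group cannot be used", that selection bias is possible and that conclusions on effectiveness are limited. It does not mention regression to the mean, and it counts profiling on baseline burnout as part of the study's key strength. The abstract's conclusion looks ahead, if the intervention succeeds, to "understanding how this intervention can help academic staff members with different initial burnout levels".

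**The concern.** The T1 burnout score does two jobs: it defines the profiles, and it is the starting value of the change compared between them. Part of any single score is measurement error or a passing state. People placed in the high profile have, on average, a positive deviation of that kind at T1, and people in the low profile a negative one. At T2 these deviations shrink, so the high profile falls and the low profile rises with no help from the course. An untreated group profiled in the same way would show this movement and allow it to be subtracted. Here there is none.

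The bias has a known direction. It favours the conclusion that the course helps most where burnout is highest, which is what a reader of RQ 1 would look for. The general caveat about the missing control group warns about the overall pre-post change. It does not tell readers that the contrast between profiles is tilted as well.

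**Working it through.** **Inputs from the article.** Single arm; profiles from T1 burnout; the same 15-item scale at each time point; three profiles in the preliminary results; 265 enrolled, of whom 113 completed (113/265 = 42.6%); recruitment target 300; median 109 and mean 123 days from T1 to T2 among completers; more dropout in the highest-burnout profiles, with no rates given.

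**Assumptions, because the article gives no figure.** True course effect zero; equal burnout variance at T1 and T2; T1-T2 correlation r from 0.6 to 0.9; test at the 5% level; profile shares 25/50/25% in the simple case. The article states no power, effect size or retest figure for this comparison, so there is none to reproduce.

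**Step 1: expected change in the high group.** Change = -(1 - r) × mean baseline z. For the top quarter, mean z = φ(0.674)/0.25 = 1.27.

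- r = 0.6: 0.4 × 1.27 = 0.51 SD fall
- r = 0.7: 0.3 × 1.27 = 0.38 SD fall
- r = 0.8: 0.2 × 1.27 = 0.25 SD fall
- r = 0.9: 0.1 × 1.27 = 0.13 SD fall

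The lowest quarter shows the mirror-image rise.

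**Step 2: how often the test rejects.** With two time points, profile-by-time is a one-way ANOVA on change. Write d for the fall in step 1. The between-group variance of change is 0.5d², the total is 2(1 - r), and the noncentrality is n × 0.5d² / [2(1 - r) - 0.5d²]. At r = 0.8 and n = 113: 0.5 × 0.254² = 0.0323; 0.4 - 0.0323 = 0.3677; 113 × 0.0323/0.3677 = 9.9. With 2 and 110 degrees of freedom this gives rejection in 80% of studies. The same formula gives 99, 95 and 47% at r = 0.6, 0.7 and 0.9. Simulation agrees:

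| r | n = 113 | n = 300 |
|---|---|---|
| 0.6 | 98.6% | 100% |
| 0.7 | 94.0% | 100% |
| 0.8 | 78.9% | 99.6% |
| 0.9 | 47.0% | 89.7% |

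Repeat runs at 113 completers differed by up to about three percentage points. The right-hand column is an upper bound, as if all 300 were measured twice. More data make the false finding more likely.

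**Step 3: a fitted three-profile analysis.** With burnout continuous, three indicators, 265 people profiled and 113 random completers, the high profile fell 0.56, 0.43 and 0.29 SD at r = 0.6, 0.7 and 0.8. False positives were 98, 94 and 77%. The result does not depend on cutting the score at quartiles.

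**Step 4: the case kindest to the plan, truly discrete and stable classes.** With three indicators, and separation in within-class SD per indicator:

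| Separation | Total r | False positives |
|---|---|---|
| 1.5 | 0.79 to 0.89 | 60% to 32% |
| 2 | 0.87 to 0.93 | 21% to 15% |
| 3 | 0.94 to 0.97 | 4% to 5% |

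The range within each row reflects within-class correlation over time of 0 or 0.5. With profiles from a single score and within-class correlation 0.5, the rate was 83, 63 and 35% at separations 1.5, 2 and 2.5.

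**Step 5: differential dropout.** With assumed completion of 50/43/34.5% in low/middle/high groups, the rates at r = 0.6 to 0.9 were 98.4, 93.0, 78.1 and 46.0%. With a heavier loss in the high group they were 96, 88, 70 and 39%. Dropout shifts the rate but does not remove the problem.

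**The case against.** The strongest reply is that the result depends on quantities the article does not give. If the profiles are distinct, stable classes with almost no misclassification, the artefact disappears (step 4, separation 3). That stands, and it rules out saying that the artefact is certain. It is not a defence either: nothing reported shows such separation, and the preliminary mention of three distinct profiles says nothing about their stability. A high correlation alone is not enough, since a continuous score at r = 0.9 still gives 47%.

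A second reply is that the authors are already cautious. This is partly right. RQ 2 speaks of observed changes, the abstract's conclusion is conditional, and Strengths and Limitations restricts claims on effectiveness. Its remark on whom the course may benefit most is tied to engagement under RQ 3. A reader might infer that the article claims throughout to show for whom the course works; it does not. The causal wording is confined to RQ 1 and the Statistical Analyses section.

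A reader might also infer three further things that the documents do not support:

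- **That every outcome is equally affected.** Stress, flexibility, well-being and procrastination do not define the profiles. They are affected only through their correlation with the T1 burnout error.
- **That the dropout comparison in RQ 3 has the same flaw.** A chi-square test on dropout has no change score to regress.
- **That people are assigned to their most likely class.** The article does not say how profile membership is carried into the ANOVA.

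**Conclusion.** The concern holds for burnout under RQ 1. Unless the profiles are very well separated and stable (in these simulations, discrete classes with a total T1-T2 correlation of about 0.94 or more), the planned comparison would tend to show improvement in the high profile and worsening in the low one with no course effect. Over assumed correlations of 0.6 to 0.9 and about 113 completers, the spurious fall in the high group is about 0.5 to 0.13 SD, and the false-positive rate is about 98 to 45%. For discrete classes the rate runs from about 60-80% at modest separation down to nominal.

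These sizes rest on assumed correlations, profile shares and a 5% level. The direction rests only on what the article states: grouping on T1 burnout, burnout change as an outcome, and no control group. As written, the burnout part of RQ 1 cannot separate a differing effect from regression to the mean.

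**What to change.** 1. In RQ 1 and the Statistical Analyses section, describe profile differences in burnout as observed change. Do not use the profile-by-time test on burnout as evidence of differential benefit.
2. Report each profile's burnout change beside the change expected from regression to the mean over a stated range of correlations, for example 0.6 to 0.9. Name this limitation in Strengths and Limitations.
3. If a test of differential burnout change is wanted, compare the between-person variance at T1 and T2 in a mixed model on all participants; hierarchical modelling is already planned for RQ 2. State that the test assumes variance would be stationary without the course, and that it cannot say which profile changed. Do not restrict it to completers: with assumed completion of 60/45/20% across low/middle/high groups, a completers-only Pitman-Morgan test had 8-10% false positives.
4. Optionally, use a profile-outcome method that corrects for classification error. It removes only the part due to misclassification.

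Moving the comparison to T2-T3 change by T1 profile is not a safe substitute. If T1 deviations are passing states that fade gradually (AR(1) decay, 123 days then about 182), that test was falsely significant in about 78, 82 and 76% of runs at r = 0.6, 0.7 and 0.8.

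The cost is revised wording, modest extra analysis and a more cautious RQ 1 conclusion. No new data are needed.

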**Results:**

As of March 2026, a total of 265 participants had enrolled in the course and given their consent to participate in the research. The current data are being analyzed, and the results are expected to be published in late 2026 or early 2027.

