#### Setting and Participants

This study is conducted at the University of Helsinki where the course is open to all university personnel, including teaching faculty, researchers, and administrative and support staff. The course has been available since fall 2023. For RQs 1 to 3, participants are recruited to attend the course via regular communications and advertisements to university personnel via university HR, intranet, email, and website. All willing participants can attend the course, and there are no exclusion criteria in the study. Participation in the research is optional, and participants can study in the course without consenting to research. At the beginning of the course, participants are asked to give or decline their permission to use their questionnaire data and written responses for research purposes.

For RQ 4, a purposive subsample (N≈30‐40) will be recruited from participants who have completed the course for semistructured interviews. Sampling will be stratified according to the latent burnout profiles identified in RQ 1 in order to include participants from each profile and permit systematic comparison of experiential patterns across profiles. Separate written consent is given for the interviews before the start of the interview.

For RQs 1 to 3, data collection started in 2023 when the course was opened to all staff members. For RQ 4, data collection is scheduled to take place in fall 2026.

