### The Course

The course “Occupational Well-being for University Staff” is based on ACT, with a central aim of enhancing participants’ skills in psychological flexibility. Training in key working life skills, such as time and effort management and reflection, is integrated into the course. The course was developed on the web-based Moodle platform and can be completed entirely online. Although it is recommended to complete the course over a 12-week period, participants are free to proceed at their own pace. The flexible schedule is an attempt to accommodate the varying time demands of academic work and allow participants to engage with the course at times that best suit their individual schedules. Participants can take the course either with a group or on their own. A group can be, for example, a research group, a team, or a unit. The small group discussions in the course work best if there are 3 to 5 people in the group, but participants can choose how to conduct this. The course is designed to function without a facilitator.

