## Results

As of the first data freeze in November 2025, a total of 265 participants had enrolled in the course and given their consent to participate in the research, and 113 participants have completed the course (Table 1). Among participants who completed the course, the mean number of days between questionnaires at T1 and T2 was 123, and the median was 109 days. The first data cut is expected to be published in late 2026 or early 2027. Preliminary results suggest that participants’ burnout scores at T1 reflect 3 distinct profiles and that the profiles experiencing the highest burnout scores are also more likely to drop out. Similarly, participants completing the course alone were more likely to drop out than those in a peer group.

**Table 1. T1:** Characteristics of the study sample recruited in the first data cut (N=265).

Background characteristics	Participants, n (%)
Job description	
Teaching and research staff	35 (13.2)
Other expert and support staff	226 (85.2)
Missing or N/A^a^	4 (1.5)
Course completion method	
Self-guided or alone	99 (37.4)
With a peer group	145 (54.7)
Missing or N/A	21 (7.9)

a N/A: not available.

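### RQ 3 tests dropout by chi-square in a self-paced, continuously open course with no participation window, so status at a data freeze cannot separate dropout from still in progress

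*Protocol article*

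**What the plan says.** Statistical Analyses fixes the RQ 3 method: "attrition analyses are conducted using chi-square tests of independence and odds ratios to examine whether dropout rates differ across latent burnout profiles". The same sentence extends the comparison to the two ways of taking the course, with a group or alone.

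The design around that test is open-ended:
- Setting and Participants: "The course has been available since fall 2023". Strengths and Limitations describes the study as continuously open.
- The Course: "Although it is recommended to complete the course over a 12-week period, participants are free to proceed at their own pace".
- Future Directions lists a predetermined participation window as something a later iteration could add, which implies that this course has none.

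Results gives the position at the first data freeze: 265 enrolled, 113 completed, and among completers "the mean number of days between questionnaires at T1 and T2 was 123, and the median was 109 days". The same paragraph reports preliminary findings that the profiles with the highest burnout scores, and participants working alone, were more likely to drop out.

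The date of that sample appears in two forms. Results has "As of the first data freeze in November 2025, a total of 265 participants had enrolled"; the Abstract has "As of March 2026, a total of 265 participants had enrolled".

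**The concern.** A chi-square test and an odds ratio need a settled yes/no status for each person, and neither can use unequal follow-up. Here follow-up at a freeze ranges from about two years for the first entrants to almost nothing for the last. Someone who enrolled six weeks before the freeze, or who is on module 5 after five months, has not completed but has not necessarily left. Being past the recommended 12 weeks (84 days) says little, because the median completer took 109 days.

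Two things are at stake. The overall dropout rate is overstated if non-completion at the freeze is read as dropout. The comparisons that RQ 3 asks about can also mix slow pace or recent enrolment with dropout. Preliminary answers are already in print, and the first data cut is due to be published in late 2026 or early 2027.

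**Working it through.** **Figures from the article.** 113/265 = 42.6% completed; 265 − 113 = 152 (57.4%) had not. Completion time among completers: mean 123 days, median 109. Formats: 99 self-guided, 145 with a peer group, 21 missing. The article states no dropout rate and no dropout count, so there is no planned figure to reproduce.

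**Assumptions.** Entry is uniform over W days. Taking entry to start between 1 September and 1 November 2023, and the freeze to fall between 1 and 30 November 2025, W runs from 731 to 821 days.

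**Recent starters.** The number enrolled within d days of the freeze is 265 × d/W:
- d = 84: 27 to 30 people
- d = 109: 35 to 40
- d = 123: 40 to 45

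**Non-completers who would still finish.** Let p be eventual completion. With mean completion time 123 days, 113 = 265 × p × (1 − 123/W), so the number pending is 113 × 123/(W − 123).
- W = 731: 13,899/608 = 22.9; p = 51.3%
- W = 821: 13,899/698 = 19.9; p = 50.2%

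That is 13% to 15% of the 152. It is probably low, because late finishers have not yet been seen and the 123-day mean is therefore cut short by the freeze. If the 113 completers belonged instead to March 2026 (W = 851 to 942), the same formula gives 13,899/728 = 19.1 to 13,899/819 = 17.0.

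**Effect on the comparison.** The scenarios simulate 99 versus 145 participants with equal eventual completion (50.5%), lognormal completion times (median 109, mean 123) and W = 790. Everyone not completed at the freeze is counted as a dropout, and tests are at two-sided 5%.

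| Difference between groups | Dropout OR | Rejection rate |
|---|---|---|
| None | 1.00 | 5.0% |
| One group 1.5 times slower | 1.19 | 9.6% |
| One group 2 times slower | 1.39 | 22.9% |
| One group entered only in last 18 months | 1.16 | 8.5% |
| One group entered only in last 12 months | 1.47 | 29.5% |

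**Candidate remedies under the same model.**
- *Log-rank or Cox on time to completion.* This corrects late entry (about 5%) but worsens the slower-pace case: about 22% rejection at 1.5 times slower, against 9% to 10% for chi-square on freeze status. A completion hazard mixes pace with eventual completion.
- *A 180-day window with matching follow-up.* This corrects late entry (OR 1.00, 5.0%), but about 15% of eventual completers take longer than 180 days even at normal pace. At 1.5 times slower it rejects about 50% of the time.
- *A 12-month window.* With σ = √(2 ln(123/109)) = 0.492, the share of eventual completers finishing by day 365 is Φ(ln(365/109)/0.492) = 99.3% at normal pace. It is Φ(ln(365/163.5)/0.492) = 94.9% at 1.5 times slower and Φ(ln(365/218)/0.492) = 85.3% at 2 times slower. Dropout is 1 − 0.505 × that share: 49.9%, 52.1% and 56.9%. The ORs against normal pace are 1.09 and 1.33. The window removes most of the distortion for a moderate difference in pace, but not for a twofold one.

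**The case against.** The article never says that people in progress are counted as dropouts. A reader might infer it from 113 completers out of 265 sitting beside a statement about who dropped out, but the other 152 are nowhere called dropouts. A cut-off rule may stand in the full protocol or analysis plan. That stands, and the point is therefore conditional on how dropout is defined.

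Statistical Analyses does not tie the planned test to the November 2025 freeze either, and Results labels its dropout findings as preliminary. That also stands. What remains is that those findings were drawn from a freeze, and that the article indicates no participation window that would give each person a final status.

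A reader might go further and take the preliminary profile and format differences to be artefacts. The documents do not support that. With equal pace and entry dates the test keeps its 5% level and only the overall rate is inflated. The article gives neither pace nor entry date by group. A 1.5-fold difference in pace also moves the OR little against sampling error: the SE of the log OR with 99 versus 145 is about 0.26, and ln 1.19 = 0.17.

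Finally, chi-square is not wrong in itself. Once dropout has a fixed window and everyone analysed has been followed that long, it is a valid test. That stands and shapes the fix.

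**Conclusion.** The concern holds in conditional form. The article fixes a yes/no dropout test for a course without a common end point, and reports preliminary dropout differences from a calendar freeze. Raw status at that freeze cannot separate dropout from still in progress.

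If freeze status is what is used, about 20 to 23 of the 152 non-completers are misclassified and completion is understated by roughly 8 to 9 percentage points (42.6% against 50.2% to 51.3%). This rests on uniform entry since fall 2023 and on the observed 123-day mean. Bias in the odds ratios needs a further condition, a difference between groups in pace or calendar entry. In the scenarios examined, the null OR then moves to between 1.16 and 1.47.

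Separately, and on the face of the text, N=265 carries two dates about four months apart. Since the freeze date decides who has had time to finish, this needs one answer.

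**What to change.** - Keep chi-square tests and odds ratios for RQ 3. Define dropout as no T2 within a fixed window from each person's T1 that is long relative to observed completion times, for example 12 months. Include only participants enrolled at least that long before one stated freeze date.
- Rerun the preliminary dropout statement by profile and by format on this definition.
- Report entry dates and T1-to-T2 times by profile and format, so that readers can judge whether pace or entry differs.
- Time-to-completion curves censored at the freeze may be added as a supplement. A Cox hazard ratio should not be read as a dropout effect.
- State which date belongs to N=265 and correct the other.

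**Cost.** This is a change of wording and a rerun. T1-to-T2 intervals have already been computed, so the questionnaire dates are available. The real price is sample size at the first cut. Under uniform entry a 12-month window keeps 265 × (W − 365)/W, which is 133 to 147 of the 265 for W = 731 to 821. The people left out come back in at a later cut. A shorter window keeps more people but lets differences in pace back into the comparison.
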